## Abstract

**Background:**

Substance use is a high-impact biopsychosocial problem in Chile, where 21% of adults have experienced a severe alcohol use episode. In the past year, the prevalence rates were 12.5% for marijuana, 0.8% for cocaine, and 0.4% for cocaine base paste. Cannabis prevalence in Chile is higher than the global (4.2%) and South American (3.58%) averages. Cocaine prevalence in Chile is lower than in South America (1.62%) but higher than the global average (0.42%). No international reports are available for cocaine base paste. Mental health and substance use programs in Chilean primary care involve psychologists and social workers. Solution-focused brief interventions (SFBIs) are based on solution-focused brief therapy, a strengths-based and person-centered approach in which practitioners adopt a stance of “not being the expert,” respecting clients’ needs and perspectives.

**Objective:**

This study aims to determine whether the SFBI implemented by psychosocial teams (psychologists and social workers) for individuals with alcohol and other drug use in primary health care centers leads to better outcomes than usual care.

**Methods:**

We will conduct a randomized controlled clinical trial (ClinicalTrials.gov registration pending) comparing a 3-session SFBI (experimental group) with a single session of brief counselling as usual care (control group) in primary care. Interventions will be delivered in person by a psychologist or social worker. A total of 320 participants are expected to be recruited during preventive routine checkups using the Alcohol, Smoking, and Substance Involvement Screening Test. Participants reporting intermediate- to high-risk substance use on this screening tool will be randomly assigned to each group. Research assistants will administer instruments at baseline and at 3-, 6-, and 9-month follow-ups and will be blinded to the assigned treatments. The primary outcome assessed will be substance use patterns, while secondary outcomes include background information, depressive symptoms, anxiety symptoms, and motivation for treatment. Statistical analyses, including *t* tests, ANOVA, and Fisher exact tests will be conducted depending on variable type and normality. A qualitative component to assess acceptability and pertinence will include focus groups with participants and practitioners, followed by a content analysis.

**Results:**

Funding for this study started in April 2024. As of the submission date of this protocol, 55 practitioners from 9 primary health care centers have been trained in SFBIs. Recruitment began in February 2025, with 73 participants enrolled and 23 who dropped out. Recruitment will continue until December 2026. No analyses have been conducted to date. Findings are expected to be published during the second half of 2028.

**Conclusions:**

This study strengthens primary care by integrating targeted psychosocial interventions for substance use into existing programs, thereby enhancing real-world applicability. If effective, the intervention could be adopted into routine care and inform public policy on mental health and substance use.

**International Registered Report Identifier (IRRID):**

DERR1-10.2196/75628

## Introduction

### Overview

Substance use is a high-impact biopsychosocial problem in Chile. Chile has one of the highest levels of alcohol consumption per capita on the continent, with rates of 15% for men and 3.7% for women [1]. In addition, 21% of the population have experienced a severe alcohol episode, compared with the global average of 18% [1]. These high levels of alcohol consumption are associated with health indicators, including cirrhosis prevalence and alcohol-related causes of death [2]. Furthermore, illicit drug use in Chile showed a prevalence of 12.5% in the past year and 12.7% in the past month for marijuana (18.1% for men and 7.4% for women), 0.76% in the past year and 1% in the past month for cocaine (1.8% for men and 0.3% for women), and 0.4% in the past month for cocaine base paste (0.7% for men and 0.2% for women) [3,4]. The rates of cannabis use in Chile are concerning when compared with the global and South American prevalence. The global prevalence of marijuana is 4.12%, and in South America it is 3.58%. Cocaine prevalence is lower in Chile than in the rest of South America (1.62%) but remains higher than the global prevalence (0.42%) [5]. No international reports are available for cocaine base paste. In terms of age groups, marijuana and cocaine use is more common among individuals aged 19-25 years, whereas cocaine base paste is more prevalent among individuals aged 26-34 years [3]. Drug-related deaths have tripled in the Americas and are among the top 10 causes of disability-adjusted life years [6].

### Psychosocial Variables

Alcohol and drug use are associated with various psychosocial indicators, including domestic violence, child abuse, and anxiety-depressive disorders [7-10]. From a social perspective, the highest prevalence of alcohol and substance use disorders, including marijuana, cocaine, and cocaine base paste in Chile, is observed among populations with lower socioeconomic status [2]. In terms of the incidence of alcohol-related crime, 53% of crimes were attributed to alcohol use, and 52.9% of those arrested for drugs, crime, or domestic violence met the criteria for alcohol use disorders. Regarding drug use, a recent study showed that among individuals who have been arrested due to high social connotation crimes, family violence, and drug-related issues, urine tests were applied to 141 individuals (74.7% and 25.3% women); the results showed that 65% has consumed at least one substance, the most common being marijuana (58%), followed by cocaine (30%) [11]. Although, no data were reported regarding cocaine base paste, the same study reported that the prevalence of substance use during the past year was marijuana (48.4%), cocaine (21%), and cocaine base paste (11.4%) [11]. Finally, being a victim of theft, sexual abuse, or any harassment is associated with a higher likelihood of reporting higher quantity and frequency of alcohol consumption [12]. All these dimensions intersect with areas where the intervention of psychosocial teams in primary health care (PHC) centers plays a role in prevention, diagnosis, treatment referral, and follow-up.

### Chilean Public Policy for Substance Use

The range of treatment options for substance use in Chile includes various programs to address different patterns of use and diagnoses. In this context, PHC centers play a fundamental role. Within the framework of the National Mental Health Plan (Plan Nacional de Salud Mental) 2017-2025, a series of programs have been established for the benefit of community mental health [13]. These include the Psychosocial Support Program (Programa de Apoyo Psicosocial) in PHC, the Prevention and Treatment Program for Alcohol and Drug Use and/or Dependence (Programa de Prevención y tratamiento del Consumo y/o Dependencia de Alcohol y Drogas) in primary care, as well as the Explicit Health Guarantees Law (Garantías Explicitas en Salud), which since 2007 includes care for individuals under 20 years of age with harmful alcohol and drug use. Additionally, the Detection, Intervention, and Referral Program for Alcohol, Drug, and Tobacco Use (Programa Detección, Intervención, y Referencia de Alcohol, Drogas y Tabaco) is based on brief interventions aimed at reducing substance use and covers 150 communes throughout the country [13].

### Brief Interventions

It is worth noting that the duration and intensity of brief intervention programs for substance use and their effectiveness have been widely discussed in scientific literature. The Center for Substance Abuse Treatment from the United States asserts that most individuals in substance use treatment drop out before completing the program and recommends the incorporation of brief therapy techniques when offering treatment [14]. Furthermore, it has been suggested to provide a brief intervention for all individuals seeking treatment before referring them to long-term modalities [14]. In this context, brief interventions are described as a therapeutic relationship in which a professional provides one or more individuals with therapeutic assistance to achieve changes or goals to improve various aspects of the person’s life in the short term [15-18]. Interdisciplinary and collaborative work in PHC has shown positive results in addressing substance use. However, such interventions tend to be costly and more intensive than what is typically feasible to provide at this level of care, which may include psychiatrists, nurses, physicians, psychologists, and social workers. Moreover, their outcomes are similar to brief interventions [19]. The psychosocial approach to substance uses in PHC involves understanding that the problem of substance use is related to social determinants of health, as well as internal aspects of the individual, such as self-efficacy, coping strategies, motivation, and commitment [20,21].

In Chile, mental health and substance use programs in primary care involve psychologists and social workers, which often leads to working in pairs and, at times, overlapping daily intervention tasks. However, both professions have different focuses in their approach. While psychologists are often trained in the individual’s intrapsychic processes, social workers are trained to understand the context, family, and social factors or determinants surrounding the individual. The interdisciplinary approach, which involves collaborative work, mutual learning, and overlapping roles [22], is common in primary care due to the person-centered model promoted by the comprehensive health-care model [23].

A study conducted in Chile found no significant difference in substance use between a single-session brief intervention provided by social workers or psychologists, following the Feedback, Responsibility, Advice, Menu Options, Empathy, and Self-Efficacy approach, and the delivery of a pamphlet [24]. Despite these findings, this type of brief intervention is currently applied in Chilean PHC when individuals are detected with a moderate risk of substance use. In this context, the National Mental Health Plan stated the need to develop more outcome studies that address the needs and particularities of the Chilean health system and population [13].

### Solution-Focused Brief Interventions

Solution-focused brief interventions (SFBIs) are based on solution-focused brief therapy: a strengths-based and person-centered approach developed by clinical social workers in the United States that draws from systemic approaches and brief family therapy. Nevertheless, it is applicable to psychologists as well as social workers with clinical training, as it seeks to accompany others in processes of change. One notable aspect of this model is its cultural adaptability, as it approaches individuals participating in an intervention from a stance of “not being the expert” and respects their needs and perspectives [25]. An SFBI considers both individual aspects and interactions with significant others and the context to which individuals belong. Therefore, it is presumed to be more suitable for Latin populations, where close relationships and family ties are highly valued [26,27]. This is different from models such as Motivational Enhancement Therapy (Motivational Interviewing Treatment Context) [28], which focuses on enhancing individuals’ intrinsic motivation [29] without considering relational aspects.

In an SFBI, the process of change occurs in conversations about solutions. These conversations aim to co-construct meanings, identify exceptions to the problem, develop a preferred future (based on a miracle or a hypothetical situation where the problem no longer exists), and explore how the person or family has achieved those exceptions in the past to repeat them in the future, thereby, making the desired future possible [25]. A literature review regarding SFBIs with substance users has shown promising results in reducing substance use and psychosocial problems associated with it [30]. Our team has previously developed a linguistic adaptation of SFBIs [31], providing methodological support for its applicability to the Chilean population receiving primary care. After that study, 2 pilot implementations were conducted to examine the feasibility of the model by social workers in primary care [32,33]. The results of the pilot studies showed positive trends in terms of reducing days of abstinence, average use, and maximum number of drinks on a single occasion; decreasing alcohol-related consequences and depressive symptoms, and improving participants’ subjective well-being [32,33]. Given that (1) previous research has not shown conclusive evidence of a single-session brief intervention on reducing substance use patterns [24], (2) SFBIs have shown promising results in pilot studies with alcohol use [32,33], (3) there is an urgent need for evidence-based interventions in Chilean public PHC [13], and (4) current usual care in PHC allows for the introduction of a new methodology to be compared, conducting a randomized controlled trial of SFBIs adapted to Chilean culture and language and implemented by psychosocial teams, compared with usual brief interventions, could make a substantial contribution to the available knowledge on brief interventions for substance and the future implementation of public mental health policy addressing substance use in Chilean PHC.

### Objectives

The general objective of this study is to determine whether the SFBI implemented by psychosocial teams (psychologists and social workers) in individuals with alcohol and other drug use in PHC leads to better outcomes than usual care. Specifically, the study aims to determine whether the SFBI reduces substance use patterns and the risk level of substance use among participants at the 3-month, 6-month, and 9-month follow-ups post baseline. It also aims to determine whether the intervention reduces the consequences of substance use and improves mental health symptoms at these follow-up points. In addition, the study seeks to determine whether participants receiving the SFBI improve their substance use patterns, substance use risk level, consequences of substance use, and mental health symptoms as compared to those receiving a minimal intervention. Finally, the study explores whether psychosocial professionals implementing the SFBI, as well as the individuals who participated in the intervention group, find the model acceptable and relevant to primary care.

### Hypotheses

This study has the following hypotheses. First, participants who receive the SFBI will decrease their substance use patterns and risk-level use of alcohol, marijuana, cocaine, and cocaine base paste. Second, participants receiving the SFBI will report positive changes in the consequences associated with alcohol, marijuana, cocaine, and cocaine base paste use, as well as improvements in mental health symptoms between baseline and follow-ups. Third, when comparing outcomes between the intervention group and the usual care group, it is expected that participants in the intervention group will show greater reductions in substance use, consequences of use, and mental health symptoms than those receiving usual care. Finally, both participants and professionals involved in the intervention group will report experiences indicating that the model is acceptable and relevant for implementation in primary care.

## Methods

### Ethical Considerations

This protocol has been approved by the Research Ethics Committee of the Pontificia Universidad Católica de Chile (ID 230619010; May 30, 2024), the Research Ethics Committee of the Local Health Services at the Metropolitan South-East area (September 12, 2024), and the Valparaíso–San Antonio area (N°23/2024; December 11, 2024). This protocol has been registered in ClinicalTrials.gov (registration pending). However, it was previously registered in Open Science Framework Registries (osf.io/875pj) on November 19, 2024. The protocol presented in this study is the second version, approved by the aforementioned committees. All participants (patients and professionals) signed an informed consent document and can choose to stop participating in the study at any time without consequence for their relationship with the primary health clinic or the university.

Confidentiality and privacy of participants will be protected. Psychosocial professionals’ information is stored in the database to maintain contact with each of them during this study. This data will not be shared with anyone outside the study. Patients’ identifiable information will be stored in a key-protected folder, to which only the research coordinator will have access. An alphanumeric code will be generated automatically once the patient’s information is entered into the REDCap (Research Electronic Data Capture; Vanderbilt University) platform, where the instruments are embedded and data from each patient are stored and remain deidentified. Once the data collection phase is complete, the deidentified database will be downloaded and securely stored by the principal investigator in a password-protected digital folder for future research purposes. The deidentified database can be requested from the first author. The research team, professionals, and any research assistants hired to perform data tabulation or analysis tasks related to this study’s content will be trained to maintain confidentiality and will sign a confidentiality agreement. They will not possess printed or digital copies of the data.

Psychosocial professionals and patients participating in this study will be recorded on audio during randomly selected sessions within the first 10 months of SFBI implementation (5 sessions per professional). This data and information will be carefully stored and managed by the principal investigator; the names of recordings will be coded, and only an expert in SFBIs will listen to each recording to assess the practitioners’ fidelity to the model. The content regarding patients’ private lives will not be the focus of these analyses. Recordings of the sessions between psychosocial professionals and patients will be stored for 3 years in a digital folder owned by the principal investigator, protected with a secure password. Participants will be informed through the informed consent that their sessions may be recorded in audio, and they will be reminded of this if their session is recorded.

Patients will receive compensation each time they respond to the questionnaires. The compensation will consist of a grocery store gift card equivalent to US $5 at baseline, US $6 at the 3-month follow-up, US $7 at the 6-month follow-up, and US $8 at the 9-month follow-up. The gift cards are redeemable for food and are intended to compensate participants for the time spent answering the questionnaires.

### Study Design

The design of this study corresponds to a superiority randomized controlled clinical trial, conducted in public primary care clinics, to evaluate the effect of an SFBI and compare it with usual care, consisting of brief counseling and an educational brochure. The experimental and control groups will consist of primary care patients who report intermediate- to high-risk substance use and will be randomly assigned to each group. In addition, the acceptability and relevance of the applied intervention will be explored among participants in the experimental group using a qualitative approach, which focuses on a deep understanding of experiences considering the subjectivity and meanings attributed to them by individuals [34], through focus groups and qualitative analysis of their content. This study is guided by the SPIRIT (Standard Protocol Items: Recommendations for Interventional Trials) checklist (Multimedia Appendix 1).

### Sample Size

The necessary sample size was calculated considering the minimum effect size found in evidence-based psychosocial interventions for substance use disorders (Cohen *d*=0.24 for polysubstance use, equivalent to Cohen *f*=0.12) [35]. The calculation was performed using the G*Power (Heinrich-Heine-Universität Düsseldorf) statistical software for sample size calculation [36], considering 80% power and a significance level of 5%. For the interaction effect between within-subject and between-subject factors in mixed ANOVA (details available in the Analysis Plan section), a sample size of 96 individuals was obtained, and after considering a 40% attrition rate [24,35] in follow-up, it increases to 160 individuals. The evaluation of the SFBI will be conducted separately by substance type (evaluating its effectiveness separately for at least alcohol, cocaine, and cocaine base paste, considering possible overlaps between them and marijuana). Thus, we plan to recruit 320 participants.

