The third specific objective aims to determine whether participants receiving the SFBI improve their substance use patterns, substance use risk level, consequences of substance use, and mental health symptoms as compared with those receiving a minimal intervention. A descriptive analysis of the recorded variables will be conducted for each participant in both experimental and control groups at baseline and at 3 months, 6 months, and 9 months post baseline. Quantitative variables will be described using mean, SD, median, minimum, and maximum values, and their distribution normality will be assessed using frequency histograms and the Shapiro-Wilk normality test. Categorical variables will be described using absolute and percentage frequencies. For each posttreatment measurement (3 months, 6 months, and 9 months), the following analyses will be conducted: the change in substance use patterns and substance use risk level (TOP) will be calculated for each participant in both experimental and control groups, and the mean with its corresponding CI will be estimated; the change in the PHQ-9 score will be calculated for individuals in both experimental and control groups, and the mean with its corresponding CI will be estimated; the change in the GAD-7 score will be calculated for individuals in both experimental and control groups, and the mean with its corresponding CI will be estimated. Baseline characteristics, including demographic background and sociofamilial situation, of participants in the control and experimental groups will be compared, with *t* tests or Wilcoxon-Mann-Whitney tests used for quantitative variables when the normality assumption is unmet, and the Fisher exact test used for categorical variables. Given that this is a superiority design, 1-tailed tests will be used for the following comparisons. The mean decrease in monthly consumption will be compared between individuals in the experimental and control groups using a mixed ANOVA, with group (experimental and control) as the between-subjects factor and time of measurement (pretreatment, 3 months, 6 months, and 9 months) as the within-subjects factor. Similarly, mean PHQ-9 scores will be compared between the two groups using a mixed ANOVA, with group (experimental and control) as the between-subjects factor and time of measurement (pretreatment, 3 months, 6 months, and 9 months) as the within-subjects factor, with the Friedman-aligned ranks test applied if the variable normality assumption is unmet. Finally, the percentage of individuals who decrease their substance use patterns and risk (TOP) will be compared between the experimental and control groups, using the Fisher exact test.

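### The 80% power for d=0.24 is not supported: a two-group f=0.12 was entered as the group-by-time interaction effect, where d=0.24 gives f of about 0.05

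*Protocol article*

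**What the plan says.** The Sample Size section takes its effect from evidence-based psychosocial interventions for substance use disorders: "Cohen *d*=0.24 for polysubstance use, equivalent to Cohen *f*=0.12". It runs G*Power "considering 80% power and a significance level of 5" percent. The test powered is named: "For the interaction effect between within-subject and between-subject factors in mixed ANOVA". The result is stated as "a sample size of 96 individuals was obtained, and after considering a 40% attrition rate" the figure rises to 160. Because the intervention will be evaluated by type of substance, the section then ends: "Thus, we plan to recruit 320 participants".

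Specific Objective 3 in the Analysis Plan defines the ANOVA. It has two groups and "time of measurement (pretreatment, 3 months, 6 months, and 9 months) as the within-subjects factor". The same paragraph plans one-tailed tests for the between-group comparisons. The article states neither the correlation between visits nor a sphericity correction.

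**The concern.** Cohen's f measures the spread of means around their average, in SD units. For two equal groups compared once, each mean lies d/2 from the average, so f=d/2 and 0.24 becomes 0.12. The interaction f is a different quantity. It measures how much the group difference changes across visits, after the average difference over all visits has been removed. A group difference of 0.24 at follow-up therefore does not give an interaction f of 0.12.

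If 0.12 was entered directly as the interaction effect, the claimed 80% power belongs to an effect about twice as large as the one named. The section presents d=0.24 as the smallest effect found for such interventions, so a reader would take a null result as evidence against an effect of that size. The test would not justify that reading.

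**Working it through.** **Inputs.** From the Sample Size section: d=0.24, f=0.12, 80% power, 5% significance, N=96, 40% attrition, 320 recruits. From Specific Objective 3: k=2 groups, m=4 visits, the first pretreatment. Assumed, because not stated: equal allocation, sphericity, and a common correlation rho between visits (0.5, with 0.3 to 0.7 as the range).

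**Step 1: reproduce the plan's figure.** For a within-between interaction, lambda = f²·N·m/(1−rho), with df1 = (k−1)(m−1) = 3 and df2 = (N−2)·3.
- With f=0.12, N=96, rho=0.5: lambda = 0.0144 × 96 × 4 / 0.5 = 11.06, df2 = 282, power 0.8002.
- N=94 gives 0.791, so 96 is the smallest even total.
- 96/(1−0.40) = 160.

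Both stated figures reproduce. With f=0.12, none of the other settings tried gives 96 (m=2 or 3; rho=0, 0.3, 0.6 or 0.7; alpha 0.10). So 0.12 was evidently used as the interaction f.

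**Step 2: the interaction f that d=0.24 implies.** It is the population SD over the four visits of half the standardised group difference. Randomisation puts the expected baseline difference at 0.
- Differences (0, d, d, d): halved values 0, 0.12, 0.12, 0.12; mean 0.09; deviations −0.09, 0.03, 0.03, 0.03; f = √[(0.0081 + 3 × 0.0009)/4] = √0.0027 = 0.052, that is 0.2165·d.
- Linear build-up to 0.24 at 9 months: f = 0.045.
- 0.24 at two of the three follow-ups, 0 at the other: f = 0.060. This is the maximum for one-directional differences not exceeding 0.24.

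**Step 3: power of the planned interaction test for d=0.24.** For the constant effect at N=96 and rho=0.5, lambda = 0.0027 × 96 × 4 / 0.5 = 2.07.

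| Pattern | N | rho 0.3 | rho 0.5 | rho 0.7 |
|---|---|---|---|---|
| Constant, f=0.052 | 96 | 15% | 20% | 31% |
| Most favourable, f=0.060 | 96 | 19% | 25% | 40% |
| Constant, pooled (60% of 320) | 192 | 27% | 37% | 58% |

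A 20,000-run simulation of the constant pattern at N=96 and rho=0.5 gave 20.3%. For 80% power with that pattern and rho=0.5, about 508 completers would be needed.

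**Step 4: the effect that f=0.12 stands for.** Constant pattern: 0.12/0.2165 = 0.55 at every follow-up. Most favourable pattern: 0.12/0.25 = 0.48.

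**Step 5: a 1-df alternative, for comparison.** Take the mean of the three follow-ups, adjusted for baseline. Its variance in SD² units is (1+2·rho)/3 − rho² = 0.667 − 0.25 = 0.417 at rho=0.5.
- 48 per arm: SE = √(2 × 0.417/48) = 0.132; 0.24/0.132 = 1.82; power 44% two-sided, 57% one-sided.
- 96 per arm: SE = 0.093; ratio 2.58; power 73% two-sided, 82% one-sided.

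**The case against.** The strongest reply is that 20% is conditional. It depends on the correlation, sphericity and effect pattern, none of which the article states. That rho=0.5 reproduces 96 shows what was entered in the software, not what the data will show. This stands, so the result is given as a range. Even the best combination shown, 40%, is half of what is claimed for 96 completers.

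Second, the trial recruits 320, not 96. A reader might infer that the trial has only a one-in-five chance of detecting its planned effect. The documents do not support that. The one-in-five figure belongs to an evaluation with exactly 96 completers. The article gives no numbers per substance and allows for overlap between substances, so a common substance may have more than 96 and a rare one fewer. Pooled, 192 completers give about 37%. The Results section reports 32% attrition so far; at that rate about 218 would complete (320 × 0.68), giving about 42% at rho=0.5. Analysis is by intention to treat with multiple imputation, so the analysed set is not completers alone. All this limits the one-in-five figure, but it does not restore 80% for 96.

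Third, one-tailed tests are planned. A 3-df F test has no one-tailed form; using alpha 0.10 as a stand-in gives 30% at N=96 (constant effect, rho=0.5). Sidedness does matter for a 1-df contrast, which is why both versions are shown.

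Fourth, the source of d=0.24 is not at hand, so its standardisation is unknown. If it refers to change scores, the SD of change equals the outcome SD at rho=0.5, since √[2(1−0.5)] = 1, and the result is the same.

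Finally, it is tempting to conclude that the primary test must move to a pooled 1-df contrast. Correcting the power statement does not require that, and pooling would depart from the evaluation by substance that the Sample Size section describes.

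**Conclusion.** The statement that 96 completers give 80% power for d=0.24 on the group-by-time interaction is wrong as written. The arithmetic from f=0.12 to 96 and 160 is correct; the error lies in what f=0.12 represents. At 96 completers, a constant d=0.24 has about 20% power at rho=0.5, and the claimed 80% belongs to an effect about twice as large as the one named.

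This rests on no expected baseline difference, which randomisation supplies, and on equal allocation, sphericity and a common between-visit correlation, which are assumed. The shortfall at 96 completers holds for every pattern and correlation in the table. The finding does not show that the whole trial has 20% power, and it does not by itself call for a larger trial.

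**What to change.** **Required.** In the Sample Size section, delete the claim that 96 completers (160 recruited) give 80% power for d=0.24. Replace it with one of these:
- 96 completers give 80% power for d of about 0.55 at every follow-up (about 0.48 in the most favourable pattern), at rho=0.5 with sphericity; or
- the power for d=0.24 as a range: about 20% at rho=0.5, 15% to 31% for rho 0.3 to 0.7, and up to 40% in the most favourable pattern, with correlation, sphericity and effect pattern stated.

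This means rewording one paragraph. The stated power becomes less favourable. No extra enrolment is requested. The abstract reports that no analyses have been conducted, so the correction can be made without knowledge of results.

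**Optional.** Replace the 3-df interaction with a 1-df baseline-adjusted contrast of the follow-up mean, and state its sidedness and analysis set with its power (Step 5): 44% two-sided or 57% one-sided for 96 completers in one substance evaluation, and 73% or 82% for 192 pooled completers. Pooling across substances would change the planned evaluation by substance and would need a pooled consumption outcome that the article does not define. That is a separate decision for the sponsor.
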